### Study design

The study will start with a 10-patient prospective observational pilot study following the same entry and exclusion criteria as for the randomized trial and undergoing the same procedures. All 10 participants will receive chloroquine at the doses used in the trial; they will not be randomized. The purpose of the pilot study is to develop the study procedures for the randomized controlled trial, including the safe monitoring of participants, and to acquire some preliminary data on the safety of chloroquine in those with COVID-19 in Vietnam. Data from these patients will not be included in the final analysis. Once the pilot study has been completed, and the data reviewed by the trial steering committee (TSC), the data monitoring committee (DMC), and the Ministry of Health (MoH) ethics committee (EC), we will proceed with the trial. We aim for minimum delay between completing the pilot study and starting the randomized trial.

The main study is an open label, randomised, controlled trial with two parallel arms of standard of care (control arm) versus standard of care with 10 days of chloroquine (intervention arm) with a loading dose over the first 24 hours, followed by 300mg base orally once daily for nine days. The study will recruit patients in three sites in Ho Chi Minh City, Vietnam: the Hospital for Tropical Diseases (HTD), the Cu Chi Field Hospital, and the Can Gio COVID hospital. Additional sites including the National Hospital for Tropical Diseases in Ha Noi, Vietnam will be added based on enrolment rates.

All adult patients (≥18 years old) presenting to the study centres with positive throat/nose swabs (RT-PCR) for SARS-CoV-2 and requiring hospital admission will be eligible for study inclusion subject to the inclusion and exclusion criteria. Randomization will be stratified by severity of illness with severe disease being defined by a SpO2 ≤94%, or tachypnea (respiratory rate ≥24 breaths/min), and mild-moderate disease being defined by SpO2 >94% and respiratory rate <24 breaths/min without supplemental oxygen.

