***Randomization and treatment allocation***. Randomization will be 1:1 to either chloroquine or standard of care treatment. Randomization with variable block sizes of four and six will be used to assign subjects to treatment. Randomization will be stratified by recruiting centre and disease severity. The randomization list will be generated according to the OUCRU randomization and drug dispensing SOP. In brief, the study statistician will set up statistical code to generate the randomization list and transfer it to the central study pharmacist. The study pharmacist will change the random seed, i.e. the initialization of the random numbers generator, in the statistical code in order to blind the study statistician and then run the code to prepare the final randomization list for treatment preparation. The randomization list will be password protected and stored on a secure server to which only the study pharmacist has access. Based on the randomization list, the study pharmacist will prepare randomization envelopes and generate identical sealed treatment packs for each study ID and distribute them to the sites in batches as required. Each pack will contain sufficient chloroquine for the 10 days of treatment. Enrolment logs specific to each study site will be used to assign participants to the next available sequential number and corresponding sealed treatment pack.

***Study intervention***. Chloroquine will be administered orally, as tablets. For unconscious participants chloroquine can be crushed and administered as a suspension via a nasogastric tube. A loading dose, administered with food where possible, is given on the first study day. Following the first 24 hours, participants will receive a dose of chloroquine phosphate salt of 500mg once daily until 10 days after randomization (unless they are <53kg, when the dose will be reduced, see
Table 2).

Chloroquine has complex pharmacokinetic properties with an enormous apparent volume of distribution (200–300 L/kg) and a terminal elimination half-life of 1–2 months, so concentrations in plasma (and rapidly exchanging tissue compartments) are determined predominantly by distribution not elimination. Given that EC50 values against the SARS-CoV-2 virus are in the low micromolar range
*in vitro*, which suggests moderate activity, it is likely that relatively high concentrations will be required for maximum effects

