Biological specimens and laboratory evaluations: On study entry all participants will have a review of clinical investigations done so far. Where an investigation has been performed within the last 24 hours, the results will be recorded, and they will only be repeated if clinically indicated. Study entry laboratory tests will be performed as per the study schedule below.

***Subsequent assessments***. Participants will have daily assessment as per standard of care while in-patient by the hospital staff. While in-patient the study will collect the following data: peripheral oxygen saturation (pulse oximeter), respiratory rate, and FiO2. The use of a ventilator or other non-invasive ventilation device will be recorded each day. Participants will have clinical assessment recorded as per the trial assessment schedule (see
Table 3). The decision to discharge patients will be at the discretion of the attending physician and will depend upon the clinical status of the patient. According to current standard of care, recovery and hospital discharge is dependent upon the patient having had at least two daily consecutive negative PCR throat/nose swabs. Following discharge, participants will be seen on days 28, 42 and 56 post-randomization.

**Table 3. T3:** Trial assessment schedule.

Procedures	Screening	Enrollment/Baseline (Visit 1)	Follow-Up (Visit 2)	Follow-Up (Visit 3)	Follow-Up (Visit 4)	Follow-Up (Visit 5)	Follow-Up (Visit 6)	Follow-Up (Visit 7)	Daily visits to discharge	Day 28 visit	Day 42 visit	Final Study Visit (Day 56)
Informed consent	x											
Demographics	x											
Medical history	x											
Randomization	x											
Physical exam	x	x	x	x	x	x	x	x	x	x	x	x
Throat/nose swab for viral PCR		x	x	x	x	x	x	x	x			
Vital signs	x	x	x	x	x	x	x	x	x			
Weight		x										
CBC w/diff, plts		x		x		x		x				
Serum chemistry ^a^	x			x		x		x				
Blood store (3-5 mls)		x						x				x
ECG (as indicated) ^b*^		x										
CXR	x								x (discharge)			x
Adverse event evaluation			x	x	x	x	x	x	x	x	x	x
WHO ordinal outcome scale **									x (discharge)	x	x	x
EQ5D questionnaire **										x		x
Estimated total blood volumes ml per day ms	6–10	10–12		10–12		10–12		10–12				3–5
Total blood volume over course of study mls (both clinical and research purposes)												52–63

^a^ Urea, Creatinine, ALT, bilirubin

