Probable	There is evidence to suggest a causal relationship and the influence of other factors is unlikely.	SAR
Definitely	There is clear evidence to suggest a causal relationship and other possible contributing factors can be ruled out.	SAR

SAE, serious adverse event; SAR, serious adverse reaction.

Expectedness

If an AE or AR is not expected with COVID-19 disease or with chloroquine, then it is unexpected. An unexpected adverse reaction (UAR) is one not previously reported in the current Summary of Product Characteristics (SPC) at the time the event occurred, or one that is more frequent or more severe than previously reported. The definition of an UAR is given in
Table 4. If an SAR is assessed as being unexpected, it becomes a suspected unexpected serious adverse reaction (SUSAR).

Investigators should always check the current version of the SPC. Expected toxicities associated with chloroquine are:
Frequency unknown: Abdominal pain; agranulocytosis; alopecia; anxiety; atrioventricular block; bone marrow disorders; confusion; corneal deposits; depression; diarrhoea; eye disorders; gastrointestinal disorder; headache; hearing impairment; hypoglycaemia; hypotension; insomnia; interstitial lung disease; movement disorders; myopathy; nausea; neuromyopathy; neutropenia; personality change; photosensitivity reaction; psychotic disorder; QT interval prolongation; seizure; severe cutaneous adverse reactions (SCARs); skin reactions; thrombocytopenia; tinnitus; tongue protrusion; vision disorders; vomiting.Rare or very rare: Cardiomyopathy; hallucination; hepatitisOverdose: Overdose is difficult to treat and can result in life-threatening features including arrhythmias (which can have a very rapid onset) and convulsions (which can be intractable). Hypoglycaemia can also feature. However, treatment in this study will be directly observed as an in-patient and therefore is extremely unlikely.

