The frequency of serious and grade 3 and 4 ARs as well as the frequency of specific AEs will be summarized (both in terms of the total number of events as well as the number of participants with at least one event). The proportion of participants with at least one such event (overall and for each specific event separately) will be summarized and (informally) compared between the two treatment groups based on Fisher’s exact test if the expected number in one of the cells is at most one and the chi-square test if expected number in each cell is larger than one.

Analysis of other secondary outcomes

1. The duration of hospital stay from the time of randomization.2. The number of ventilator-free days during the first 28 days following randomization.3. The time to (all-cause) death following the first 10, 28, and 56 days since randomization.4. The WHO ordinal outcome scale for COVID-19 at days 28, 42 and 56
^24^.5. Fever clearance time.6. Development of ARDS defined by the Kigali criteria
^25^.7. Oxygenation-free days over the first 28 days.

The analyses of these secondary endpoints will be defined in the statistical analysis plan.

***Statistical hypotheses***. The primary null hypothesis is that the rate of clearance of virus from throat/nose swabs is not different between chloroquine compared with standard of care therapy.

***Analysis datasets***. The primary analysis population for all analysis is the full analysis population containing all randomized participants except for those mistakenly randomized without COVID-19. Participants will be analysed according to their randomized arm (intention-to-treat). In addition, the primary endpoint will be analysed on the per-protocol population, which will exclude the following participants: major protocol violations and those receiving less than one week of administration of chloroquine for reasons other than death.

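### The per-protocol duration rule does not name an arm, so read literally it drops every control; applied to the chloroquine arm only, it can drop early clearers

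*Protocol article*

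**What the plan says.** Under Statistics, Analysis datasets, the main population is the full analysis set, analysed by randomized arm: "The primary analysis population for all analysis is the full analysis population containing all randomized participants except for those mistakenly randomized without COVID-19". A second population is then added: "In addition, the primary endpoint will be analysed on the per-protocol population". It leaves out participants with major protocol violations and "those receiving less than one week of administration of chloroquine for reasons other than death". The second limb names no arm and has one exemption, death.

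Four other statements bear on it:

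- Allocation (Study procedures): "Randomization will be 1:1 to either chloroquine or standard of care treatment". The control arm has no chloroquine.
- Dosing length (Study procedures, Study intervention): "participants will receive a dose of chloroquine phosphate salt of 500mg once daily until 10 days after randomization". Each pack holds the full course.
- Place of dosing (Safety reporting, Expectedness): "treatment in this study will be directly observed as an in-patient".
- Discharge (Subsequent assessments): the attending physician decides, but under current standard of care "recovery and hospital discharge is dependent upon the patient having had at least two daily consecutive negative PCR throat/nose swabs". Two consecutive negative swabs are also what defines viral clearance in the primary endpoint.

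After discharge, the next scheduled visits are days 28, 42 and 56. Nothing says whether chloroquine stops or continues when a patient leaves hospital before day 10.

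**The concern.** There are two separate problems.

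**The rule cannot be run as worded.** A control has zero days of chloroquine, and the reason is allocation, not death. Every control meets the exclusion.

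**The sensible reading selects on something linked to the outcome, in one arm.** If only chloroquine patients are judged, membership of the per-protocol set depends on how long each was treated after randomization. Clearing virus opens the way to discharge. If dosing ends there, a chloroquine patient who clears quickly falls short of a week and is dropped, while a control with the same clearance time stays in. The faster chloroquine works, the more of its own early responders would go.

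At stake is the only alternative population named for the primary endpoint, the one readers would use to judge whether the main result is robust to non-adherence.

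**Working it through.** **Inputs from the protocol.** Clearance time log-normal, mean 2.17 and SD 0.74 on the natural log scale; 240 patients, 1:1, so 120 per arm; design factor 0.76; log-rank test and Cox model (Statistics). Assumed here because the article does not state them: two-sided 5% level, no censoring.

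**The plan's own figure.** Standard error of the difference in mean log time = SD × √(4/N).

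- N = 240: 0.74 × √(4/240) = 0.0955; −ln 0.76 = 0.274; 0.274/0.0955 = 2.87; power = Φ(2.87 − 1.96) = 82%.
- N = 120: 0.74 × √(4/120) = 0.135; −ln 0.68 = 0.386; 0.386/0.135 = 2.85; power = Φ(2.85 − 1.96) = 81%.

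Both agree with the stated 80%, so the model is read correctly.

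**Literal reading.** Controls remaining = 120 − 120 = 0. No comparison exists.

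**Chloroquine arm only: which clearance times give under one week?** Assume daily swabs and discharge on the day of the second negative. Virus gone between days 3 and 4 gives negatives on days 4 and 5 and discharge on day 5. Gone between days 4 and 5 gives discharge on day 6.

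- If a week means seven dosing days (days 0 to 6) and a dose is given on the discharge day, discharge on day 5 falls short and day 6 does not. The cut-off is clearance before day 4.
- If a week means seven elapsed days, discharge on day 6 also falls short. The cut-off is clearance before day 5.

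**Share of the chloroquine arm that clears before the cut-off c.** Φ((ln c − 2.17 − ln f)/0.74), where f is the true factor.

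- f = 1: day 4, Φ(−1.06) = 14%; day 5, Φ(−0.76) = 22%.
- f = 0.76: day 4, Φ(−0.69) = 25%; day 5, Φ(−0.39) = 35%.

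**Effect on the comparison.** Simulation of 5,000 trials per scenario, dropping the stated fraction of early clearers from the chloroquine arm only. A hazard ratio above 1 favours chloroquine.

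| True factor | Early clearers who stop drug at discharge | Chloroquine arm excluded (day 4 / day 5) | HR for clearance | Significant for chloroquine | Significant against chloroquine |
|---|---|---|---|---|---|
| 1 | none | 0% | 1.00 | 3% | 2% |
| 1 | half | 7% / 11% | 0.93 / 0.89 | under 1% | 9% / 14% |
| 1 | all | 14% / 22% | 0.86 / 0.79 | under 1% | 19% / 40% |
| 0.76 | none | 0% | 1.40 | 74% | 0% |
| 0.76 | half | 12% / 17% | 1.26 / 1.21 | 41% / 28% | 0% |
| 0.76 | all | 25% / 35% | 1.11 / 0.98 | 10% / 2% | under 1% / 3% |

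**The case against.** The strongest reply is that the selection route is never stated. The protocol plans dosing to day 10 and packs a full course. Neither viral clearance nor discharge is listed among the reasons for discontinuation. Two negative swabs are necessary for discharge, not sufficient. The sentence about observed in-patient dosing is there to explain why overdose is unlikely; it is not an instruction to stop at discharge, and it fits equally well with patients staying in for the whole course. If dosing continues to day 10, this bias is zero. All of that stands, and it is why the first row for each true factor in the table matters as much as the last.

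A reader might infer that the rule does in practice remove the fastest clearers, that the per-protocol analysis is therefore biased against chloroquine, and that it reverses a true benefit. The documents do not support this. The mechanism is possible, not established. Those dropped would also include patients who stop for arrhythmia, other adverse events, progression or withdrawal, and the simulation does not model them. Reversal appears only in the ratio of geometric mean times when all early clearers stop (1.04 to 1.16 at a true 0.76). Under the planned Cox model the hazard ratio is then 1.11 to 0.98, which is attenuation or loss of the benefit. Nor can it be inferred that the trial's main result is compromised, because that result comes from the intention-to-treat analysis.

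It is also fair to say that nobody would knowingly empty the control arm, and that an analysis plan, not shown here, may refine the populations. But the protocol fixes this rule itself. Naming the arm repairs only the first problem: the rule would still act on one arm and exempt only death.

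**Conclusion.** The point holds in this form: the duration limb excludes every control if followed literally. If confined to the chloroquine arm, it can selectively exclude early clearers there. Depending on how many early clearers stop at discharge, the per-protocol hazard ratio with no true effect lies between 1.00 and 0.79, with false significance against chloroquine in up to about 40% of trials. At the design factor it lies between 1.40 and 0.98.

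These sizes rest on the plan's log-normal model, discharge on the day of the second negative swab, a cut-off at day 4 to day 5, no censoring, and exclusions made up of early clearers only. The stopping fraction is unknown, so no single figure can be given.

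This should be fixed for the sake of the supportive analysis. It does not threaten the primary one.

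**What to change.** Reword the per-protocol definition in Analysis datasets, and carry it into the analysis plan before database lock:

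1. State that the treatment-duration limb applies to participants allocated chloroquine.
2. Judge adherence only over doses due before the earliest of viral clearance, discharge or death, so that early clearance or discharge is never itself a reason for exclusion. Any adherence threshold is the sponsor's choice.
3. Count a control as off protocol only for receiving chloroquine or for a major violation, with major violations judged by the same criteria in both arms.
4. Reconcile the statements under Study intervention, Subsequent assessments and Expectedness on whether dosing continues after discharge. Which of them is right is for the investigators to say.

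The cost is a short change of wording, and the article reports only two participants enrolled. The rule needs dose dates on the case report form. The assessment schedule in Table 3 has no dosing row, so this should be confirmed, not assumed. Even when reworded, the analysis would still drop chloroquine patients who stop early for toxicity, so it should continue to be read as supportive.

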### Data management

***Data collection and entry***. Source documents are where data are first recorded, and from which participants’ CRF data are obtained. These include, but are not limited to, hospital records (from which medical history and previous and concurrent medication may be summarised into the CRF), clinical and office charts, laboratory and pharmacy records, radiographs, and correspondence. CRF entries will be considered source data if the CRF is the site of the original recording (e.g. there is no other written or electronic record of data).

Data collection is the responsibility of the clinical trial staff at the site under the supervision of the site PI. The investigator is responsible for ensuring the accuracy, completeness, legibility, and timeliness of the data reported. All trial data will be recorded on to paper CRFs and will be entered into CliRes, a 21 CFR Part 11-compliant data capture system hosted by the OUCRU IT department. The participants will be identified by a unique trial specific number and/or code in any database. The name and any other identifying detail will not be included in any trial data electronic file. The data system includes password protection and internal quality checks, such as automatic range checks, to identify data that appear inconsistent, incomplete, or inaccurate.

***Record retention***. CRFs, clinical notes and administrative documentation will be kept in a secure location and held for 15 years after the end of the trial. Clinical information will not be released without written permission, except as necessary for monitoring, auditing and inspection purposes. During this period, all data should be accessible to the competent authorities with suitable notice. Electronic data will be kept for at least 20 years at the OUCRU CTU.

***Publication and data sharing policy***. The Trial Mamagement Group (TMG) will maintain a list of all investigators and OUCRU staff part of the OUCRU COVID research group. This research group will be cited in the authorship list and the full list presented in the acknowledgements section at the end of the paper. This list will include investigators who contributed to the investigation being reported but who are not members of the writing committee. In principle, substudy reports should include all investigators for the main study, although in some instances where a smaller number of investigators have made any form of contribution, it may be appropriate to abbreviate the listing. All headline authors in any publication arising from the main study or sub-studies must have a made a substantive academic or project management contribution to the work that is being presented. “Substantive” must be defined by a written declaration of exactly what the contribution of any individual is believed to have been. In addition to fulfilling the criteria based on contribution, additional features that will be considered in selecting an authorship group will include the recruitment of participants who contributed data to any set of analyses contained in the manuscript and/or the conduct of analyses (laboratory and statistical), leadership and coordination of the project in the absence of a clear academic contribution.

In line with Wellcome Trust policy that the results of publicly-funded research should be freely available, manuscripts arising from the trial will, wherever possible, be submitted to peer-reviewed journals that enable open access via UK PubMed Central (PMC) within six months of the official date of final publication. All publications will acknowledge the trial's funding sources. In line with research transparency and greater access to data from trials OUCRU’s clinical trials are registered at ClinicalTrials.gov (
NCT04328493, 31/03/2020) and a data sharing policy is in place. This policy is based on a controlled access approach with a restriction on data release that would compromise an ongoing trial or study. Data exchange complies with Information Governance and Data Security Policies in all of the relevant countries.

### Quality assurance and quality control

***Risk assessment***. The quality assurance (QA) and quality control (QC) considerations have been based on a formal risk assessment, which acknowledges the risks associated with the conduct of the trial and how to address them with QA and QC processes. QA includes all the planned and systematic actions established to ensure the trial is performed and data generated, documented and/or recorded and reported in compliance with the principles of ICH GCP and applicable regulatory requirements. QC includes the operational techniques and activities done within the QA system to verify that the requirements for quality of the trial-related activities are fulfilled.

***Central monitoring at OUCRU CTU***. Data from each site collected on the paper CRFs will be double entered and stored on a central database in OUCRU. This database will be checked at OUCRU CTU for missing or unusual values (range checks) and checked for consistency within participants over time. If any such problems are identified, the site will be contacted and asked to verify or correct the data. OUCRU CTU will also send reminders for any overdue and/or missing data with the regular inconsistency reports of errors. Other essential trial issues, events and outputs will be detailed in the Data Management, Monitoring and Quality Management Plans that are based on the trial-specific risk assessment.

***On-site monitoring***. A site initiation visit will be conducted for each study site by staff from the OUCRU CTU. All essential site staff including the PI, lead pharmacist and lead research nurse must be in attendance. The initiation training will include training in the administration of trial treatment, as well as the trial procedures. Monitoring will then be carried out approximately annually at each site by OUCRU CTU staff. On site monitoring will also be regularly conducted by the site monitors. The frequency, type and intensity of routine monitoring and the requirements for triggered monitoring will be detailed in the Monitoring Plan, which will also detail the procedures for review and sign-off. The monitoring will adhere to the principles of ICH GCP and the Monitoring Plan.

